### Statistical analysis

All analyses will be conducted in accordance with the intention-to-treat (ITT) principle. After randomization, participants will be labelled with a research code consisting of a unique number. This unique number will be used for the data analysis, to guarantee blind analysis of the data by the researcher. Baseline data and data regarding primary and secondary outcomes will be presented using descriptive statistics. Differences in baseline data between the intervention and control group will be assessed using Student’s *t*-test for continuous data and the *χ*^2^-test for categorical data. A p-value ≤ 0.05 will be considered statically significant.

#### Primary study parameter

For the primary outcome measure (RTW), the number of days until RTW (either full or partial) will be analysed using a Kaplan-Meier survival method. The patients who dropped out of the study will be censored. The differences between the intervention and the control group will be tested using a log rank test. If significant differences between the intervention and control groups are found with regard to the prognostic variables, the outcome variable RTW will be adjusted for these variables in a multivariate Cox regression analysis. In addition to the ITT analysis aimed at ‘all—cause return to work’, the analysis will be performed excluding those patients who died during follow-up and those who have a life expectancy of less than a few months, because they will not RTW.

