### Randomization

When the researcher has received the baseline questionnaire, the patient will be randomized to 1) the intervention group that will receive tailored work-related support, or 2) the control group that will receive care as usual. A computerized randomization programme ALEA [24] will be used to do this. As patients differ between the participating hospitals in terms of diagnosis, demographic factors and age, and because these factors are important prognostic factors for RTW [25], randomization will be stratified for gender, age (age groups: 18–54 and 55–63 years) and hospital, so as to prevent bias due to unequal randomization. Minimization will be applied to equalize group sizes. The patients, healthcare professionals and researchers will not be blinded for the group assignment.

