### Sample size

The calculation of the sample size is based on two earlier studies, because no recent data are available on the RTW of GI cancer patients from clinical patient cohorts. Data from 2005 on 220 GI cancer patients, provided by a large occupational health service in the Netherlands, show that two years after diagnosis, 63 % of patients had returned to work full-time [27]. Based on these data, it is hypothesized that the percentage of 63 % RTW in GI cancer patients is the maximum result of ‘care as usual’. In a study by Nieuwenhuijsen [28], an intervention group of 35 radiotherapy patients received a supportive work-related intervention in a hospital. RTW was measured between the end of curative treatment and the first day of (partial) work resumption. This was found to be 89 % after twelve months. The median time between enrolment and the end of treatment was 42 days. Earlier studies at the AMC show that the percentage of patients that RTW in the first 42 days is around 8 % [29, 30]. The RTW for the intervention group was therefore set at 89 %–8 % = 81 %.

The sample size is calculated using the Power and Sample Size Calculation program nQuery Advisor 7.0. A power of 80 % and a p value of <0.05 indicated that we should include a total of 216 patients, with a follow-up of twelve months, to indicate a difference of 81 % (intervention) versus 63 % RTW (care as usual). Allowing for a 20 % loss to follow-up and a 10 % one-year mortality rate, 309 patients should be included.

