#### Prognostic factors

The prognostic factors include age, gender, marital status (married/single/cohabiting/widowed/divorced), education (seven categories), diagnosis (primary GI cancer diagnosis: oesophagus, stomach, liver, pancreas, biliary, small intestine, colon or rectum), treatment type (surgery, radiotherapy, chemotherapy, hormonal therapy, other) and treatment duration assessed with the self-reporting questionnaires. Fatigue is measured using the Multidimensional Fatigue Inventory questionnaire (MFI) [39], with 20 items divided into five sub-scales: general fatigue, physical fatigue, reduced activity, reduced motivation and mental fatigue. The sub-scale scores range from 4 to 20; a higher (implies 20) score indicates greater fatigue. Depression is measured using the scale developed by the Centre for Epidemiologic Studies for Depression (CES-D) [40], scored with 20 items. The scores range from 0 to 60; a higher (implies 60) score indicates greater depressive symptoms weighted for the past week. Cognitive functioning is measured with the Cognitive Symptom Checklist-Work, Dutch Version (CSC-W DV), containing 19 items, with the sub-scales for working memory and executive function. Scores range from 0 to 100, with higher scores indicating more cognitive symptoms (i.e., more limitations) in the work context. This questionnaire has been translated and a customized version of the Cognitive Symptom Checklist-Work (CSC-W) [41] validation article will be published.

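### The primary log-rank test uses none of the three factors on which allocation is balanced, so it stays valid but is somewhat conservative and gives up power

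*Protocol article*

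**What the plan says.** Under Randomization, "randomization will be stratified for gender, age (age groups: 18–54 and 55–63 years) and hospital". The reason given is that patients at the participating hospitals differ in diagnosis, demographic factors and age, and "because these factors are important prognostic factors for RTW". The same section adds: "Minimization will be applied to equalize group sizes".

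Under Primary study parameter, days to RTW are described by Kaplan-Meier and "The differences between the intervention and the control group will be tested using a log rank test". No stratum or covariate is attached to that test. Adjustment by Cox regression is conditional: "If significant differences between the intervention and control groups are found with regard to the prognostic variables", RTW is adjusted for the variables that differ.

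The section Prognostic factors defines the variables that the rule can act on: "The prognostic factors include age, gender, marital status", followed by education, diagnosis, treatment and several symptom scales. Hospital is not in the list.

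**The concern.** Design and analysis treat the same factors differently. Allocation is balanced on gender, age group and hospital so that prognostic differences do not fall unevenly between the arms. The primary test then proceeds as if allocation had been simple.

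Balancing on a prognostic factor reduces the true trial-to-trial variation of the arm comparison. A log-rank test that ignores the factor still counts that variation in its variance, so under the null hypothesis it rejects less often than 5%. When there is an effect, leaving out a prognostic factor also pulls the overall hazard ratio towards 1. Both cost power.

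The conditional Cox rule does not repair this. The factors that are deliberately balanced are the least likely to differ significantly at baseline. Age in years could still differ within the two age bands, but gender and age group should rarely trigger the rule. Hospital cannot trigger it as written. At stake is efficiency in the primary comparison, in a trial planned at 80% power.

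**Working it through.** **1. The plan's own sample size.** Inputs from Sample size: 81% versus 63% RTW, 80% power, 5% level; two-sided is assumed, as the section does not say. With mean proportion 0.72, the two-proportion formula gives

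n = [1.96·√(2·0.72·0.28) + 0.842·√(0.81·0.19 + 0.63·0.37)]² / 0.18² = 96.5, so 97 per arm (194 in total).

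The continuity correction gives

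(96.5/4)·[1 + √(1 + 4/(96.5·0.18))]² = 107.3, so 108 per arm.

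That is 216, as in "A power of 80 % and a p value of <0.05 indicated that we should include a total of 216 patients". Inflation: 216/(1 − 0.30) = 308.6, so 309. Both stated figures reproduce.

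**2. The planned effect on the hazard scale.** Assuming proportional hazards, HR = ln(1 − 0.81)/ln(1 − 0.63) = ln 0.19/ln 0.37 = 1.67. Expected events are 216 × 0.72 = 155.5. Log-rank power by Schoenfeld's formula is Φ(√155.5/2 × ln 1.67 − 1.96) = Φ(1.24) = 0.89. This is the benchmark with no prognostic factors. It exceeds 80% partly because of the continuity correction and partly because a time-to-event test is more efficient than comparing two proportions.

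**3. Simulation.** 216 patients; Pocock-Simon minimisation on gender, age group and hospital, with the favoured arm chosen with probability 0.8; exponential RTW times; censoring at 12 months; no dropout. Assumed, because the article text does not give them: 4 or 8 equal-sized hospitals, equal splits on gender and age group, and the strength of each factor. Strength is written as the HR for gender and for age group (the same value for each) and the SD of the hospital log-hazard. 4,000 runs per cell; both tests applied to the same data. The Cox model contains arm, gender, age group and hospital.

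| Strength (HR; SD) | Hospitals | Null rejection: log-rank / Cox | Power: log-rank / Cox | Loss (points) |
|---|---|---|---|---|
| none (1; 0) | 4 | 0.048 / 0.052 | 0.888 / 0.891 | 0.3 |
| none (1; 0) | 8 | 0.046 / 0.050 | 0.894 / 0.896 | 0.2 |
| weak (1.25; 0.2) | 4 | 0.046 / 0.057 | 0.868 / 0.887 | 1.9 |
| weak (1.25; 0.2) | 8 | 0.042 / 0.054 | 0.869 / 0.890 | 2.1 |
| moderate (1.5; 0.3) | 4 | 0.043 / 0.055 | 0.842 / 0.885 | 4.3 |
| moderate (1.5; 0.3) | 8 | 0.035 / 0.050 | 0.845 / 0.888 | 4.3 |
| strong (2; 0.5) | 4 | 0.029 / 0.051 | 0.750 / 0.886 | 13.6 |
| strong (2; 0.5) | 8 | 0.031 / 0.065 | 0.757 / 0.887 | 13.0 |

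The Monte Carlo standard error is √(0.05·0.95/4000) = 0.003 for a null rejection rate and √(0.87·0.13/4000) = 0.005 for power. A separate simulation with 6 hospitals gave 0.90 versus 0.90 (none), 0.876 versus 0.890 (weak, 1.4 points) and 0.840 versus 0.880 (moderate, 4.0 points).

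**4. What the power figures hold fixed.** HR 1.67 is held within each combination of factors. Averaging 1 − 0.37^exp(lp) for usual care and 1 − 0.19^exp(lp) for the intervention over the factor combinations, where lp is the centred log-hazard of each combination, gives overall RTW of 63% versus 80% (weak), 63% versus 79% (moderate) and 62.5% versus 77% (strong). Part of the fall in log-rank power is therefore this dilution of the overall contrast. The null rejection rates do not depend on it.

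**5. The form of adjustment matters.** A log-rank test stratified on the full gender × age × hospital cross-classification (3,000 runs per cell, same four strengths) had power 0.83–0.85 with 4 hospitals and 0.78–0.80 with 8. Sparse strata cost information even when the factors have no effect.

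**The case against.** The strongest reply is that this is a matter of efficiency, and a modest one. In every weak or moderate setting the plain log-rank test keeps more than the planned 80% power, and with weak factors its error rate is close to nominal. That stands, and it limits the severity.

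A second reply is that a condensed article may leave stratification of a log-rank test to an analysis plan that is not shown. That has some force for the silence on strata. It has none for the adjustment rule, which the article states outright and which is badly matched to the allocation method.

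A third is that the remedy has a cost of its own. The adjusted Cox test ran at 5–6.5% under the null. The 6.5% (strong factors, 8 hospitals) is well beyond simulation error, so part of the apparent power gain in that cell reflects mild anti-conservatism. This stands and affects how the fix is worded.

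Four stronger readings are tempting but unsupported:
- A reader might infer that the primary test is invalid. It is not; the error is on the conservative side.
- A reader might infer that confidence intervals for the primary outcome are too wide. The article specifies no interval for that outcome; its stated interval is for the secondary 12-month relative risk.
- A reader might infer that the article calls hospital itself prognostic. It names diagnosis, demographic factors and age, and brings in hospital because patients differ between hospitals on these.
- A reader might infer that the missing strata leave the trial underpowered. At a smaller effect than planned (HR 1.5, 310 patients, three further prognostic scores), simulation gave 60.5% unadjusted and 65.6% adjusted. The strata account for about 5 points of that, and HR 1.5 is not the planned effect.

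**Conclusion.** The mismatch is real and lies in stated rules: allocation is balanced on three factors, the primary test uses none of them, and the conditional Cox model is unlikely to bring in gender or age group and cannot bring in hospital. The direction is secure. The size is not, because the documents do not give prognostic strength and the article text shown does not give the number of hospitals. At the planned effect the loss is nil if the factors do not predict RTW, about 1–2 points of power if weak, 4–5 if moderate and 13–14 if strong. Only the strong case (0.75–0.76) falls below 80%, and that figure also depends on reading the planned HR as holding within factor levels. This is a worthwhile improvement in efficiency, not a defect of validity.

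**What to change.** Replace the significance-triggered rule with one prespecified primary analysis:

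- **Preferred:** the arm effect in a Cox model with gender, age group and hospital as covariates, small hospitals pooled by a rule fixed before the data are seen. Pooling should limit the slight excess over 5% seen with many hospital terms. State that the hazard ratio is conditional on these factors.
- **Alternative:** a log-rank test stratified on few strata, such as pooled hospital. It leaves gender and age group unused, so it can be expected to recover only part of the loss.
- Keep the unadjusted log-rank test as a sensitivity analysis.
- Do not stratify on the full gender × age × hospital cross-classification.

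The cost is analysis wording only. The three variables are already held for randomisation, no extra patients or data are needed, and the article reports that recruitment is still under way, so the change can be made before results are seen.

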The aim of the *first meeting* is to inform patients about the importance of work during and after treatment, to identify any work-related problems, and to make a plan for the RTW (Table 1). The meeting will be scheduled before the start of the treatment and will take the form of an individual face-to-face meeting lasting approximately 30 min.

The *second meeting* aims to inform and evaluate the goals of the first meeting. This meeting will be scheduled after the first meeting, in consultation with the patient and the supporting healthcare professional (depending on the diagnosis/treatment and preferences of the patient). It will take place no more than three to six months after the first meeting. It will take the form of an individual face-to-face meeting and last about 30 min (Table 1). At the end of the meeting, the healthcare professional will evaluate whether the work-related support being provided is sufficient (on the basis of the decision diagram and the patient’s answers). If the support proves to be insufficient, the type of support will be adjusted.

The *third meeting* will consider the same issues as the second meeting: evaluating the goals of the first and second meetings. This meeting will also be scheduled at the request of the patient and/or the supporting healthcare professional at the second meeting, depending on diagnosis/treatment and the preferences of the patient, and in a maximum of six to nine months after treatment (Table 1).

In the support C-type intervention (multidisciplinary meeting), the oncological occupational physician will first hold a face-to-face meeting with the patient before the multidisciplinary meeting. The team will subsequently confer to discuss the outcomes identified by the oncological occupational physician with respect to RTW possibilities and restrictions. The oncological occupational physician will lead the multidisciplinary team consultation and is designated to provide the patient with feedback in a further face-to-face or telephone meeting.

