### Outcome measures and prognostic factors

Data on the primary and secondary outcomes, as well as prognostic factors such socio-demographic factors (i.e. age, gender, level of education), disease-related factors and work-related factors, will be gathered using five questionnaires: baseline (T0) and three (T1), six (T2), nine (T3) and twelve (T4) months after baseline. It will take approximately 30 min to complete a questionnaire. The primary outcome measure is RTW, defined as the time to a partial or full RTW, and measured as the number of calendar days between the first day of sick leave and the first day at work. The patient must have returned to work (part-time or full-time) for at least four successive weeks (independent of the number of contract hours). The secondary outcome parameters are work ability, work limitations, quality of life, RTW (yes/no) and direct/indirect costs.

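### Covariate adjustment of return to work hangs on significant between-arm differences, so strong baseline predictors usually go unused, the adjusted estimate depends on the data, and post-randomisation variables are not excluded

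*Protocol article*

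**What the plan says.** In the protocol article, Statistical analysis, the arms are to be compared at baseline: "Differences in baseline data between the intervention and control group will be assessed" by t-test or chi-square test. The threshold follows: "A p-value ≤ 0.05 will be considered statically significant".

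Under Primary study parameter, the unadjusted comparison carries no condition: "The differences between the intervention and the control group will be tested using a log rank test". Adjustment is conditional: "If significant differences between the intervention and control groups are found with regard to the prognostic variables, the outcome variable RTW will be adjusted" for the differing variables, by Cox regression.

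The Prognostic factors section names age, gender, marital status, education, diagnosis, treatment type, "treatment duration assessed with the self-reporting questionnaires", and then fatigue, depression and cognitive functioning. Outcome measures and prognostic factors says that these data "will be gathered using five questionnaires: baseline (T0) and three (T1), six (T2), nine (T3) and twelve (T4) months after baseline".

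The Randomization section stratifies on gender, two age groups and hospital, and calls diagnosis, demographic factors and age important for RTW. Patients are randomised once the baseline questionnaire is in. Of the first intervention meeting the article says: "The meeting will be scheduled before the start of the treatment".

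**The concern.** A between-arm p-value at baseline measures how uneven a particular randomisation happened to be. It does not measure whether the variable predicts RTW, which is the reason to adjust. The rule therefore selects covariates on the wrong criterion. It also works against the trial's own design: the factors used to balance the arms are those least likely to differ significantly, so they will hardly ever enter the model.

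Two further gaps follow from the wording. When the trigger fires, there are two analyses of the primary outcome and no stated order between them. And the trigger refers to the prognostic variables without limiting them to T0, although the list contains a variable that cannot be known at T0 and the questionnaires continue to T4.

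At stake are precision that the trial could have without recruiting anyone extra, and an adjusted estimate whose covariates should be known before the data are seen.

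**Working it through.** **1. The plan's own figures.** Comparing 81% with 63%, two-sided 5% level, 80% power, continuity-corrected: 108 per arm, 216 in total. This matches the Sample size section. Attrition: 216 / (1 − 0.30) = 308.6, so 309, which also matches. The sizing uses no covariates.

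**2. Design hazard ratio.** Under proportional hazards, 81% against 63% at twelve months gives ln(1 − 0.81) / ln(1 − 0.63) = ln 0.19 / ln 0.37 = 1.67 (above 1 means faster RTW).

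**3. How often a given predictor is used.** With a 5% test under randomisation, a baseline variable is selected about 5% of the time and omitted about 1 − 0.05 = 95% of the time, whatever its strength. In simulation the strong predictor entered in 4.4–5.3% of runs. Age and gender enter less often still. Hospital cannot enter, because it is not on the list.

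**4. How often a Cox model is triggered.** The list has 10 constructs. Counting the five fatigue and two cognition sub-scales separately gives 15 tests. Without age and gender these become 8 and 13. For k independent tests the chance of at least one p ≤ 0.05 is 1 − 0.95^k:

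- k = 8: 34%
- k = 10: 40%
- k = 13: 49%
- k = 15: 54%

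Correlation between the sub-scales lowers the 13-test figure. With assumed correlations of 0.3, 0.5 and 0.7 among the eight fatigue, depression and cognition scores, it becomes 46%, 42% and 37%.

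**5. Power and type I error.** Simulation with 216 patients, twelve-month censoring, 2,000 runs per setting and eight independent baseline covariates. One is strong (log-HR 0.3 or 0.6 per SD); the other seven have log-HR 0.15. All covariate effects are assumptions. Entries are rejection rates for log-HR 0.3 / 0.6.

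| Conditional HR | Unadjusted | Triggered | Pre-specified |
|---|---|---|---|
| 1.00 | 4.4% / 5.4% | 4.2% / 5.2% | 4.9% / 5.5% |
| 1.50 | 60.5% / 49.7% | 61.4% / 51.2% | 68.7% / 66.7% |
| 1.67 | 81.5% / 72.4% | 81.8% / 73.8% | 88.6% / 86.4% |

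At the design HR, the gain of the fixed set over the triggered rule is 88.6 − 81.8 = 6.8 points, or 86.4 − 73.8 = 12.6 points. The unadjusted and triggered verdicts differ in 1–2% of null trials and in 3–5% of trials with an effect. With weaker assumed predictors (down to log-HR 0.2 per SD) the gain shrinks to about 1 point. Across log-HR 0.2 to 0.6, power at HR 1.67 is about 72–89% unadjusted or triggered and about 86–90% pre-specified.

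**6. Order of events.** Baseline questionnaire, then randomisation, then the first meeting, then treatment. Treatment duration therefore arises after randomisation. Fatigue or depression at T1–T4 does too, and these could respond to the intervention.

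**The case against.** The log rank test is always run, and nothing says that the Cox model replaces it. A reader might infer that chance imbalance settles which analysis decides the trial. The text does not go that far; it only fails to rank the two.

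The rule does no visible harm to validity. Type I error stays near 5% in all three analyses, and the trigger costs essentially no power against the unadjusted test. The gap to the pre-specified model is a forgone efficiency gain that the sample size never counted on. That is right, and it limits the point to precision and pre-specification. A reader who infers an inflated false-positive rate would be mistaken.

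Saying that half of such trials would trigger a Cox model takes 13 independent tests. Counting constructs, or allowing for correlation, gives a lower figure, so only the range is defensible.

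The only between-arm tests specified are on baseline data, so a baseline reading of the trigger is natural. The article also gives no route by which up to three meetings of about 30 minutes would change how long cancer treatment lasts. A reader might infer that the planned analysis is biased by treatment duration. The documents support only that the wording permits a post-randomisation covariate and that adjusting for one can bias the effect.

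What survives is that the selection rule is written into the article, so this is not a detail left to an analysis plan, and nothing in its favour has been shown.

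**Conclusion.** The point holds as a flaw in a stated rule. Significance-triggered adjustment omits any given predictor about 95% of the time, almost never uses the age and gender factors that the trial balances on, and can never use hospital. In roughly 34–49% of such trials it yields a second, unranked analysis with covariates picked by chance.

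The cost is efficiency and a data-dependent adjusted estimate. At the design effect a fixed baseline set gains from about 1 point of power with a weak predictor to about 13 points over the triggered rule with a strong one.

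These power figures rest on assumed covariate effects, proportional hazards, independent covariates and 216 patients with complete twelve-month follow-up. They also take 1.67 as the conditional hazard ratio. If 81% against 63% is read as the marginal contrast, unadjusted power is not below the design level and adjustment adds to it. The direction is the same either way.

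The post-randomisation issue is an ambiguity to close, not a demonstrated bias.

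**What to change.** - Delete the baseline significance tests and the conditional trigger. Present baseline data descriptively.
- Name one primary analysis: a Cox model for time to RTW with arm, gender, age, hospital and a short fixed list of T0 predictors already collected, for example diagnosis and baseline fatigue. Report it whatever the baseline table shows.
- Keep the unadjusted log rank test and Kaplan-Meier curves as supportive, and say so.
- State that only baseline values may be covariates, which excludes treatment duration and all T1–T4 measurements.

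The support class (A, B or C) could be added, but it would mean applying the decision diagram to control patients, and the fix does not need it.

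Cost: analysis wording only, with no change to sample size or data collection. The primary hazard ratio becomes conditional on the covariates instead of marginal, which should be noted when it is reported. The change should be made before outcomes are seen by arm.

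### The additional return-to-work analysis excludes patients by death and short life expectancy, both arising after randomisation, and so deletes observed events and departs from intention to treat

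*Protocol article*

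**What the plan says.** The protocol article, under Primary study parameter, analyses time to partial or full RTW by Kaplan-Meier with a log-rank test. On censoring it says: "The patients who dropped out of the study will be censored". It then adds a second analysis to the intention-to-treat one, "excluding those patients who died during follow-up and those who have a life expectancy of less than a few months", and justifies it by saying these patients will not go back to work.

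Four other places bear on this:

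- Statistical analysis: "All analyses will be conducted in accordance with the intention-to-treat (ITT) principle".
- Sample size: "Allowing for a 20 % loss to follow-up and a 10 % one-year mortality rate, 309 patients should be included".
- Outcome measures and prognostic factors: RTW counts once the patient has been back, part-time or full-time, for at least four successive weeks.
- Study population and Randomization: patients are treated with curative intent at entry, and patients, professionals and researchers all know the allocation.

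The article does not say how a death before RTW enters the main Kaplan-Meier analysis.

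**The concern.** Both exclusion criteria arise after randomisation. Death during follow-up does so by definition. A short life expectancy should mostly emerge later, because entry requires curative intent. Removing patients on such grounds leaves two groups that are no longer those formed by randomisation.

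The life-expectancy criterion adds to the problem. The article gives it no cut-off in months, no time of assessment and no assessor, and none of the listed measures records it (cancer stage is the nearest). In an unblinded trial, such a judgement could depend on the arm.

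The justification is also not true in general. Four weeks at work is enough for the event, so a patient can meet the outcome in month 5 and die in month 11. The exclusion would delete that observed primary event.

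At stake are the RTW percentages from this analysis and, if mortality or prognosis differs by arm, the comparison between arms.

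**Working it through.** **1. The plan's own figures.** Inputs from Sample size: 81% versus 63%, 5% significance, 80% power, 20% loss to follow-up, 10% mortality. Taking the test as two-sided with equal arms, the two-proportion formula gives 97 per arm (194) without continuity correction and 108 per arm with it, so 2 × 108 = 216, as stated. Then 216 / (1 − 0.20 − 0.10) = 308.6, rounded up to 309, as stated. The product form 216 / (0.80 × 0.90) = 300 does not match. The sample size is therefore not in error, and the plan counts deaths as attrition added to loss to follow-up.

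**2. Patients removed for death.** 0.10 × 310 = 31, plus an unknown number for life expectancy.

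**3. RTW events deleted.** Assume constant, independent hazards over one year, the same 10% mortality in both arms, and 63% and 81% as the RTW risks in the absence of death.

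- Death hazard: d = −ln(0.90) = 0.105.
- RTW hazards: r = −ln(0.37) = 0.994 (control) and −ln(0.19) = 1.661 (intervention).
- RTW before death: r/(r + d) × (1 − exp(−(r + d))).
- Death before RTW: d/(r + d) × (1 − exp(−(r + d))).

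| | Control | Intervention |
|---|---|---|
| RTW, all randomised | 60.3% | 78.0% |
| Death before RTW | 6.4% | 4.9% |
| RTW, then death (10% minus row above) | 3.6% | 5.1% |

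The last row is the share of each arm whose observed RTW would be deleted. It is larger in the intervention arm although mortality is equal, because more patients there have returned before they die.

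**4. RTW level after exclusion, same model.** Control: (0.6031 − 0.0361) / 0.90 = 0.630. Intervention: (0.7795 − 0.0505) / 0.90 = 0.810. The exclusion overstates RTW among all randomised patients by 2.7 and 3.0 points. The difference between arms is 18.0 points against 0.7795 − 0.6031 = 17.6 points.

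**5. A less favourable assumption.** Suppose instead that 63% and 81% are the true percentages among all randomised patients and that a share D dies before RTW, with no later deaths. Exclusion then gives p / (1 − D).

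| D, both arms | Control | Intervention |
|---|---|---|
| 5% | 66.3% | 85.3% |
| 10% | 70.0% | 90.0% |
| 15% | 74.1% | 95.3% |

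If both arms truly had 63% RTW but 5% and 15% died before it, exclusion would show 0.63/0.95 = 66.3% against 0.63/0.85 = 74.1%. That is a spurious gap of about 8 points, in favour of the arm with more deaths. The planned effect is 18 points.

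**6. Conditional check on the main analysis.** If deaths are censored in the Kaplan-Meier analysis, then under the model in step 3 one minus Kaplan-Meier estimates 63% and 81%, where 60.3% and 78.0% actually return. The relative risk changes little: 0.81/0.63 = 1.286 against 0.7795/0.6031 = 1.293. Under the assumption in step 5 with D = 10%, one minus Kaplan-Meier gives 67.7% and 88.3% against true values of 63% and 81%.

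**The case against.** The strongest reply is that the exclusion is supplementary. The intention-to-treat comparison is kept and comes first, and the article itself sets the extra analysis apart from it. That stands, and it limits the seriousness. It also makes the conflict with the general intention-to-treat statement partly one of wording, though as written that statement admits no exception.

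Second, a cut-off for life expectancy may be in the full protocol, and the article says that coded data keep the analysing researcher blind. No place says that unblinded staff decide who is excluded; the arm-dependence is a possibility, not a documented fact. But a definition elsewhere would not cure selection on death itself, and coded data do not blind whoever makes a prognostic judgement at the hospital.

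Third, under independent hazards and equal mortality the contrast barely moves (18.0 against 17.6 points). That is correct. It is also the favourable case: patients too ill to work are likely to be those at higher risk of death.

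Three stronger readings are tempting and are not supported:

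- **That the main analysis censors deaths and so overstates RTW.** The article states censoring only for patients who dropped out. Counting mortality as attrition in the sample size makes censoring of deaths plausible, but it is not stated. If patients who die stay in the risk set to 12 months as not returned, there is no overstatement.
- **That the primary test is invalid.** Even with deaths censored, the log-rank test validly compares cause-specific RTW hazards; only the level of the curve is affected.
- **That the bias carries into the relative risk and the cost-effectiveness ratio.** No section says that either uses Kaplan-Meier rates, and RTW as yes/no is listed as a separate secondary outcome.

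**Conclusion.** The point holds for the additional exclusion analysis. It selects on events after randomisation, uses a criterion the article does not define, and rests on a reason that fails for patients who return and later die.

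Its size, at the plan's 10% mortality: about 31 of 310 patients removed, with observed RTW events deleted in about 3.6% of control and 5.1% of intervention patients. RTW is overstated by about 3 points per arm under constant, independent hazards, and by 7 and 9 points if all the deaths come before RTW. The documents give neither the hazards nor mortality by arm, so these figures are illustrations; the direction is the same under both assumptions.

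For the main analysis only a conditional statement is justified: if deaths are censored, one minus Kaplan-Meier overstates the share returning by about 3 points per arm under the same hazards.

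This should be corrected before the analysis, but it does not threaten the primary comparison.

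**What to change.** 1. Remove the analysis that excludes patients who died or have a short life expectancy.
2. Keep every randomised patient and treat death before RTW as a competing event: report the cumulative incidence of RTW by arm beside the log-rank and Cox results. If a simpler supplementary check is preferred, use the proportion alive and returned to work at 12 months among all randomised patients. That check counts a patient who returns and then dies as a failure, so it answers a slightly different question.
3. State in one sentence how a death before RTW enters the Kaplan-Meier analysis.
4. State that the 12-month relative risk and the denominator of the cost-effectiveness ratio use all randomised patients or the cumulative incidence, not one minus Kaplan-Meier.

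The cost is analysis wording. The planned exclusion already requires knowing who died; the competing-event analysis also needs the date. The downside is that reported RTW percentages will be slightly lower, by about 3 points per arm under the constant-hazard model.
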